## 4.2 Endpoints

### Primary endpoint:

#### SD and MD dose-escalation phases

1. The primary endpoint for safety will be observed toxicity assessed using the US National Cancer Institute common terminology criteria for adverse events version 3 (CTCAEv3). Dose limiting toxicities (DLT) will be recorded, and maximum tolerated dose (MTD) will be determined according to the criteria described in [12.1.1](#) and [12.1.2](#).

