## 5.2 Rationale for trial design

A cautious approach is recommendable when starting FHD trials with biologics. If feasible, the dose should be selected based on calculations using the “minimal anticipated biological effect level (MABEL)” approach. Due to lack of preclinical in vivo models and predictive in vitro models this has not been possible. However, a low and presumed safe first single dose has been rationalised from the lack of toxicity in the toxicology studies at all dose levels, combined with simulated human pharmacokinetics of 109-0012 and resulting IL-20 serum concentrations.

All subjects in each dose cohort will be randomised and there will be a time interval of at least 24 hours between dosing of all subjects in each dose cohort of the SD dose-escalation phase. Subjects will be monitored at the research facility during the first 24 hours. Before continuing to the next dose level, safety data for all subjects through trial Day 15 as well as PK data for all subjects through trial Day 15 will be evaluated by the Study Safety Group (See Section [12.6](#)).

All four subjects in each dose cohort can be dosed on the same day during the MD dose-escalation phase. During the MD dose-escalation phase subjects will be monitored continuously for the first 8 hours after the first drug administration. The second dose should be administered on trial Day 15, the third dose on trial Day 29, and the fourth and last dose will be given on trial Day 43. Subjects will be monitored in-house at the research facility for 4 hours after the second, third and fourth dose.

The dose-escalation decision in the MD dose-escalation phase will be made based on safety data from all subjects obtained through trial Day 57, two weeks after the last dose, as well as PK data through trial Day 57. [Table 5-1](#) shows the proposed doses and dose intervals for the dose-escalation phases and the relative time points for starting each cohort.

The MD dose-escalation phase will be performed in parallel with the SD phase, but the first dose cohort of the MD dose-escalation phase will not commence until the third dose cohort of the SD phase has been evaluated by the Study Safety Group ([Table 5-1](#)). This means that the first accumulated multiple dose has been covered by the single doses already administered. This trial design is considered both safe and efficient.

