| 1 of 4                                                                                   | Enter four subjects (3+1) at the same dose level as the current level where the toxicity event occurred.                                                                                                                                                                                                                                                                                                                                                                                                                                                                                                                        |
| 1 of 8                                                                                   | Enter four subjects (3+1) at the next dose level, according to Table 5–1 .                                                                                                                                                                                                                                                                                                                                                                                                                                                                                                                                      |
| ≥2                                                                                       | 
The dose-escalation will be stopped at this level, and no further increase of dose will occur. There will however be the possibility to add four (3+1) subjects at one or maximally two different dose levels between the current dose limiting level and the previous dose level.
 
 
• The maximum tolerated dose (MTD) is the highest dose level below the maximum administered dose (MAD) where none or 1 subjects experience a DLT.
 
• The maximum administered dose is the highest dose given in the trial.
 
• The maximal feasible dose is 3 mg/kg.
 
 |

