#### 12.1.1 Definition of dose limiting toxicities

Grade 3 AEs or higher will represent Dose Limiting Toxicities (DLT), except when the relationship to trial product is judged as unlikely.

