#### 12.1.2 Definition of maximum tolerated dose and maximum administered dose

The maximum tolerated dose (MTD) is the highest dose level below the maximum administered dose (MAD) where none or 1 subjects experience a DLT.

The maximum administered dose is the highest dose given in the trial.

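### The MTD is defined by none or one DLT with no number treated, so a level passed on 0 of 4 that later has one DLT still qualifies at 1 of 4

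*Protocol*

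**What the plan says.** Section 12.1.2 and the last row of Table 5-2 define the MTD as the highest level below the MAD "where none or 1 subjects experience a DLT". Section 12.1.2 adds: "The maximum administered dose is the highest dose given in the trial". Neither place says how many subjects must have been treated.

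The decision rows of Table 5-2 do carry numbers. With no event, the next level opens. With 1 of 4: "Enter four subjects (3+1) at the same dose level as the current level where the toxicity event occurred". With 1 of 8: "Enter four subjects (3+1) at the next dose level, according to" Table 5-1. With two or more, escalation stops.

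Section 12.1.1 defines the event without a time window: "Grade 3 AEs or higher will represent Dose Limiting Toxicities (DLT), except when the relationship to trial product is judged as unlikely". Section 5.2 decides escalation on "safety data for all subjects through trial Day 15" in the single-dose (SD) phase, and in the multiple-dose (MD) phase makes the decision "based on safety data from all subjects obtained through trial Day 57". Follow-up continues to Day 106 (SD) and Day 148 (MD) under sections 8.1.1 and 8.1.2.

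Naming the MTD is part of the primary endpoint of the escalation phases. Section 4.2 says that the "maximum tolerated dose (MTD) will be determined according to the criteria described in" sections 12.1.1 and 12.1.2. Under the Summary and section 5.3 the MTD is then the dose of the expansion phase, in which 26 subjects receive active drug four times.

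**The concern.** The escalation rows and the MTD sentence use different standards for a single DLT. Before the cut-off, one DLT among four subjects is not enough to move on, and a second cohort is required. After the cut-off, the same count at a level already left behind triggers nothing. The 1 of 4 row speaks of the current level, and the safety-based extra cohort in section 12.6.1 attaches to the cohort last performed. The passed level therefore keeps its place as an MTD candidate on half the evidence that Table 5-2 would have required had the event come earlier.

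At stake is the evidence behind the expansion dose. A late DLT is plausible, because the half-life is expected to be 15-20 days (section 5.3) and 91 days of follow-up remain after either cut-off.

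**Working it through.** The protocol gives no operating characteristic for its MTD rule, so there is no stated figure to reproduce. The check has a textual part and an illustrative calculation.

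**1. Rules side by side.**

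| DLTs at a level | Seen by the cut-off (Table 5-2) | Seen after the level was passed |
|---|---|---|
| 0 of 4 | escalate; qualifies as MTD | qualifies |
| 1 of 4 | add a 3+1 cohort at this level | no row applies; qualifies under 12.1.2 |
| 1 of 8 | escalate; qualifies | qualifies |
| 2 or more | stop; does not qualify | does not qualify |

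The two columns differ only in the 1 of 4 row.

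**2. Late window.** SD: 106 − 15 = 91 days. MD: 148 − 57 = 91 days.

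**3. Example.** MD level 4 (1.0 mg/kg) has 0 of 4 at Day 57 and is passed. Level 5 (2.0 mg/kg) has two DLTs, and escalation stops. One level 4 subject then has a related grade 3 event between Day 57 and Day 148. Level 4, at 1 of 4, is the MTD by the text.

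**4. Chance per tested MD level.** Assumptions not in the protocol: 3 active subjects at risk per cohort, no placebo DLTs, total DLT risk p per active subject, and share f of that risk falling after Day 57. Three values of f are used:
- Exposure share after Day 57 with four doses 14 days apart, one compartment and instant absorption: f = (r + r² + r³ + r⁴)/4, where r = 2^(−14/half-life). Half-life 15 days: r = 0.524, f = 0.254. Half-life 20 days: r = 0.616, f = 0.343.
- Risk even over days: f = 91/148 = 0.615.

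P(no early DLT and exactly one late DLT in 3) = 3pf(1 − p)².

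| p | f = 0.25 | f = 0.34 | f = 0.615 |
|---|---|---|---|
| 0.05 | 0.034 | 0.046 | 0.083 |
| 0.10 | 0.061 | 0.083 | 0.149 |
| 0.20 | 0.096 | 0.131 | 0.236 |
| 0.33 | 0.111 | 0.151 | 0.273 |
| 0.50 | 0.094 | 0.128 | 0.231 |

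For p = 0.10 and f = 0.25: 3 × 0.10 × 0.25 × 0.81 = 0.061.

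**5. Chance per trial.** The level must also be the highest one that qualifies. Five MD levels were simulated (400,000 runs per setting), with Table 5-2 applied to DLTs through Day 57 and section 12.1.2 to DLTs through Day 148. There were no discretionary or in-between cohorts, and SD levels were not candidates. The event counted is an MTD at a level below the last one given, with no early and one late DLT in a single cohort. Exact enumeration over the five levels agrees within about 0.1 percentage point. Each cell gives f = 0.25, 0.34, 0.615.

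| Assumed DLT risk, MD levels 1-5 | MAD = 3.0 mg/kg SD (literal) | MAD = highest MD level given |
|---|---|---|
| 1, 2, 5, 10, 20% | 1.7, 2.1, 2.8% | 6.3, 8.5, 15.4% |
| 1, 1, 2, 3, 5% | 0.05-0.08% | 2.1-5.2% |
| 2, 5, 10, 20, 33% | 5.9, 7.5, 10.5% | 10.6, 14.4, 26.0% |

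The literal reading gives less because the MAD then lies above every MD level, so MD level 5 can itself be the MTD. The path then needs level 5 not to qualify or not to be reached.

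**6. What a second cohort would add.** The chance of at least one further DLT in 3 active subjects is 1 − (1 − p)³: 27% at p = 0.10 and 49% at p = 0.20.

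**The case against.** The MTD sentence stands in the same table as the numbered rows. On cut-off data, a level below the stopping level can have been passed only at 0 of 4 or 1 of 8, so none or one is a fair summary of those outcomes. This stands and confines the point to late DLTs.

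The 1 of 4 row governs going to a higher dose, whereas naming an MTD concerns continued use of the same dose. A stricter rule for the first is no contradiction. This also stands: a reader might infer that section 12.1.2 and Table 5-2 contradict each other, and they do not. The two standards simply do not match for the same count.

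The event would probably be noticed. MD levels start 10 weeks apart (Table 5-1), so the next level's Day 57 review falls about 10 + 8 = 18 weeks after a level's first dose, when about 10 of the 13 weeks of its late window have passed. The Study Safety Group reviews all safety data and may add cohorts (section 12.6.1). The expansion starts only if the safety profile is found acceptable, on unblinded data (Summary, sections 5.1 and 5.4). That is a real condition on starting the expansion. It is qualitative, however, and does not change how the MTD is named: section 12.1.2 still says that a level at 1 of 4 qualifies.

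The larger trial-level figures depend on reading the MAD within the MD phase, although section 12.1.2 speaks of the whole trial. If the SD phase is completed, the MAD is 3.0 mg/kg, and the smaller figures are the ones to lead with.

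**Conclusion.** The point holds as a minor one that is cheap to improve. A DLT appearing after a level was passed on 0 of 4 leaves that level eligible as MTD at 1 of 4, and no stated rule requires the second cohort that Table 5-2 would have required before the cut-off.

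With the MAD read literally, this decides the MTD in about 2-3% of trials for risks of 1-20%, under 0.1% for 1-5%, and 6-10% for 2-33%. It reaches 6-15%, 2-5% and 11-26% only if the MAD is read within the MD phase. All of these rest on assumed risk curves and late shares. The top of each range assumes risk spread evenly to Day 148 although exposure is falling.

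A reader might take these as chances that the expansion runs at a dose that is too toxic. The documents do not support that: the figures count how often the MTD rests on 1 of 4, and many such levels would be acceptable. With the literal MAD, a second cohort would show another DLT and change the MTD in 0.4-0.7%, about 0.01% or less, and 2.6-4.7% of trials for the three curves.

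**What to change.** In section 12.1.2 and Table 5-2, replace the MTD sentence with wording such as this:

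*The MTD for the expansion is the highest MD dose level below the MAD with no DLT in one completed 3+1 cohort, or at most one DLT across two completed 3+1 cohorts, over follow-up to Day 148. DLTs in replaced subjects count. If a late DLT leaves the candidate with one DLT in a single cohort, the next lower qualifying level is used, unless the Study Safety Group chooses to add one 3+1 cohort within the cap of 8.*

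State alongside it whether the MAD is the highest dose in the MD phase or in the whole trial. Counting completed cohorts, rather than fixed totals of 4 and 8, fits the replacement rule in section 6.5, under which five subjects may be treated in one cohort.

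The expansion starts only after both escalation phases are completed (section 5.3), so the full count should be at hand when the MTD is named. Using the next lower level needs no enrolment and no delay, but the expansion dose may be one level lower. Choosing the extra cohort costs four subjects and about 8 weeks (to Day 57) to 21 weeks (to Day 148).

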## 12.2 Collection, recording and reporting of adverse events

All events meeting the definition of an AE must be collected and reported. At each contact with the trial site (visit or telephone, excluding safety visits, where the subject is not seeing the Investigator or his staff (e.g. visits to the laboratory)), the subject must be asked about adverse events e.g.: “Have you experienced any problems since the last contact?”

All AEs, either observed by the Investigator or reported by the subject, must be recorded by the Investigator and evaluated.

Sponsor's assessment of expectedness is done according to the reference documents: Novo Nordisk investigational product (Anti-IL-20 (109-0012) 100 mg/vial): IB, 1st Edition, and any updates hereof.

The Investigator should record the diagnosis, if available. If no diagnosis is available the Investigator should record each sign and symptom as individual adverse events.

All adverse events must be recorded by the Investigator on the standard adverse event form. If more than one sign or symptom is to be reported, use a separate adverse event form for each sign and symptom. For serious adverse events, the safety information form must also be completed.

The Investigator must report initial information on all serious AEs to Novo Nordisk within **24 hours** of obtaining knowledge about the event to:

Product Safety Surveillance Group. [contact]

The Investigator must complete the adverse event form in the EDC application and the safety information form on the paper CRFs. The Investigator must forward electronically/fax/courier copies of the safety information form to Novo Nordisk within **5 calendar days** of obtaining knowledge about the serious adverse event.

The sponsor must inform the regulatory authorities and independent ethics committee (IEC)/institutional review boards (IRB) in accordance with the local requirements in force and International Conference on Harmonisation Good Clinical Practice (ICH GCP) .

The sponsor will notify the Investigator of trial product related suspected unexpected serious adverse reactions in accordance with the local requirements. In addition, the Investigator will be informed of any trial related procedure SAE which may warrant a change of any trial procedure.

Investigators will be notified of trial-related SAEs in accordance with the local requirements in force and ICH GCP .

The monitor must be informed accordingly.

### 12.2.1 Medical events of special interest

Events such as medication errors (e.g. wrong drug administration, overdose or wrong route of administration) and suspected transmission of an infectious agent via a trial product are always to be considered as medical events of special interest.

Medical events of special interest must always be reported to International Product Safety (IPS) on adverse event form and safety information form irrespective of seriousness within the same timelines as SAEs.

### 12.3 Follow-up of adverse events

During and following a subject's participation in a clinical trial, the Investigator/institution should ensure that adequate medical care is provided to the subject for any adverse events, including clinically significant laboratory values related to the trial. The Investigator/institution should inform the subject when medical care is needed for adverse events of which the Investigator becomes aware.

The follow up information should only include new (updated and/or additional) information that reflects the situation at the time of the Investigator's signature.

All non-serious AEs classified as severe or possibly/probably related to the trial product must be followed until the subject has recovered and all queries have been resolved. However, cases of chronic conditions can be closed with an outcome of "recovering" or "not recovered". **If subjects die from another event**, these cases can be closed with an outcome of "recovering" or "not recovered".

All other non-serious AEs must be followed until the outcome of the event is "recovering" (for chronic conditions), or "recovered" or until the end of the post-treatment follow-up stated in the protocol, whichever comes first, and until all queries related to these AEs have been resolved. **If subjects die from another event**, these cases can be closed with an outcome of "recovering" or "not recovered".

The Investigator must ensure that the worst case severity and seriousness is kept consistent. The Investigator must record follow-up information on non-serious adverse events by updating the adverse event form in the EDC application.

The Investigator must forward follow-up information on serious adverse events within 5 calendar days of obtaining the information. This must be done by updating the adverse event form in the EDC application and/or completing the safety information form on paper CRF and forwarding these to Novo Nordisk.

All serious adverse events must be followed until the outcome of the event is recovered, recovered with sequelae or fatal and until all queries have been resolved. For cases of chronic conditions and cancer or if the subject dies from another event follow-up until the outcome categories are “recovered”, ”recovered with sequelae” or ”fatal” is not required, as these cases can be closed with an outcome of “recovering” or “not recovered”.

After access to the EDC application is removed, the Investigator must record any SAE follow-up information, if required, on the paper CRFs provided at study closure.

## **12.4 Pregnancy**

Women of child-bearing potential are not allowed to participate in the trial.

## **12.5 Precautions/over-dosage**

Anti-IL-20 (109-0012) 100 mg/vial has not previously been used in humans and therefore no experience with overdose and overdose reactions exists. In case of an overdose of Anti-IL-20 (109-0012) 100 mg/vial, treatment should be suspended and symptomatic medical treatment according to the clinical condition should be applied. No antidote exists in case of overdose of Anti-IL-20 (109-0012) 100 mg/vial.

Any overdose should be reported as an AE, with or without clinical manifestations, see [12.2.1](#).

## **12.6 Safety committees**

### **12.6.1 Internal Novo Nordisk safety committee**

Novo Nordisk will establish an internal safety committee to perform ongoing safety surveillance. The safety committee may recommend unblinding of any data for further analysis. If so, an independent ad hoc group will be established to maintain the blinding, since unblinded subject data will be sent from IVRS.

A Study Safety Group will be established according to Novo Nordisk standard operating procedure with the responsibility to evaluate all safety data during the SD and MD dose-escalation phases, and to determine if progression to the next dose level can be supported. The Study Safety Group will also have the mandate to add another cohort other than for safety reasons, if relevant. The Study Safety Group will consist of:

- Head of Clinical Pharmacology (chair)
- Responsible Clinical Pharmacology Scientist/International Trial Manager
- Local Medical Director
- International Medical Officer

- Safety Surveillance Advisor from International Product Safety
- Representative from Department of DMPK & Bioanalysis

A summary report with safety and PK data will be distributed to members of the Safety Group and a meeting will be set up. The decisions taken at the meeting will be documented in minutes, and distributed to Safety Group members, investigators, Chairman for the Safety Committee, relevant Project Vice President and other relevant persons.

#### SD, dose-escalation phase

The safety summary report for the decision on dose-escalation in the SD dose-escalation phase will contain information on laboratory safety data, AEs including local tolerability, vital signs, ECG evaluations and subject related information for all subjects in the dose cohort through trial Day 15, as well as PK data through trial Day 15. In line with other safety laboratory analyses, acute phase cytokine response (IL-1 $\beta$ , IL-6, TNF- $\alpha$ , INF- $\gamma$ ) and homocystein and adiponectin response in the first 24 hour post dosing period must be available for the Safety Group meetings to be included as part of the overall safety evaluation prior to escalation to the next cohort.

PK data will be presented in such a manner that unblinding of the Safety Group is avoided.

#### MD, dose-escalation phase

The safety summary report for the decision on dose-escalation in the MD dose-escalation phase will contain information on laboratory safety data, AEs including local tolerability, vital signs, ECG evaluations and subject related information for all subjects in the dose cohort through trial Day 57, as well as PK data through trial Day 57. PK data will be presented in such a manner that unblinding of the Safety Group is avoided.

Sites must not proceed to the next dose level with the new dose cohort before the recommendation from the Novo Nordisk Study Safety Group to escalate has been issued. The Study Safety Group can also recommend to stop further dose-escalations, or to add another cohort (N=3+1) of patients to the last performed dose cohort based on safety (see [Table 5-2](#)) or due to inconclusive PK and/or clinical data. Dose cohorts in-between existing dose levels can also be added (see [Table 5-2](#)). Maximally 8 subjects can be treated at the same dose level.

